Currently 200 patients are diagnosed each year in the Forth Valley Intermittent Claudication clinic. A sample size calculation carried out using GPower3 [17], indicates that to carry out a (2) group by (2) time mixed ANOVA to detect a small effect size (0.2) with an alpha of 0.05, and a power of 80%, the trial would require 26 participants in each condition. A small effect size of 0.2 was selected in the sample size calculation based on a previous study of an exercise program for physical activity in patients with IC which measured walking outcomes using pedometers [18]. The sample size calculation was based on the conservative initial (2) time point (baseline to 4 month) mixed ANOVA to increase the likelihood that the study was adequately powered to identify an initiation of walking behaviour change. A (4) time point mixed ANOVA sample size calculation required fewer participants in the study, and therefore the larger, initial (2) time point, more conservative sample size calculation was used. The sample size calculation was based on changes in the primary outcome measure. As this is a pilot study, a further aim is to determine the effect sizes achieved in the secondary outcome measures, to help inform the sample size calculation for a larger, more definitive study. Based on a previous study with patients from this population recruited at outpatient clinic, we estimate that 25% of people may decline to participate in the study. Likely attrition rate from the study for this population is unknown, therefore we have estimated a 10% attrition rate during the trial. We therefore aim to invite 80 patients to participate in the trial, of whom we expect 60 to agree to participate, and a further 6 to drop-out during the course of the trial. Based on typical numbers presenting at the clinic who are diagnosed with claudication, recruitment is estimated to take place at the rate of 2 participants/week.

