### Analysis

Data will be analysed using an intention to treat protocol in a repeated measures mixed design (2 groups*2 time points for short-term outcome, and 2 groups*4 time points for long-term outcome). Our aim is to determine the effect size achieved by this pilot to inform the sample size calculation for a larger, multi-centre study. Between-group differences in uptake of surgery will be measured using a chi-square test.

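### The long-term (2*4) analysis is labelled intention to treat, but the method named for it is a mixed ANOVA; unless values are imputed or a likelihood model is used, it would cover completers only

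*Protocol article*

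**What the plan says.** The Analysis section of the protocol article sets out the principle and the layout: "Data will be analysed using an intention to treat protocol in a repeated measures mixed design", with "2 groups*2 time points for short-term outcome, and 2 groups*4 time points for long-term outcome". It does not use the word ANOVA.

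The sample-size text under Recruitment does. It sizes the trial on a group-by-time mixed ANOVA with two time points and reports that "the trial would require 26 participants in each condition". It then says of the longer layout: "A (4) time point mixed ANOVA sample size calculation required fewer participants in the study".

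The same text expects loss. It calls the likely rate unknown and continues: "therefore we have estimated a 10% attrition rate during the trial". Of 60 recruited, 6 are expected to be lost, which leaves 54 against the 52 required.

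Outcomes are taken at baseline, 4 months, 1 year and 2 years. The Background presents the separation of starting to walk more from keeping it up as a strength of the design. The Framework and Analysis sections say that the pilot's effect size will inform the larger trial.

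**The concern.** Intention to treat means that participants are analysed as randomised, without leaving people out because of what happened later. A classical between-within ANOVA works on a complete rectangle of participants by visits. Someone who wears the pedometer at baseline, 4 months and 1 year but misses the 2-year week has no complete row, so the three observed weeks drop out of the 2*4 analysis too. The label and the named method therefore do not fit together for anyone with a missed visit, and the plan expects such people.

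The 2*4 analysis carries the claim about maintained change. Participants for whom the walking plan did not work, or who became unwell, may be the likelier ones to miss later weeks. If so, the maintenance estimate describes a selected group, and a selected estimate could pass into the design of the larger trial.

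**Working it through.** **1. Is the named method really a classical mixed ANOVA?**

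Inputs from Recruitment: effect size 0.2, alpha 0.05, power 80%, two groups. Assumptions: 0.2 is Cohen's f; the correlation between visits is ρ = 0.5; sphericity holds. The article states none of these three.

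For the group-by-time F-test with m visits and N participants in total:

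λ = f² · N · m / (1 − ρ), df1 = m − 1, df2 = (N − 2)(m − 1).

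- m = 2, N = 52: λ = 0.04 × 52 × 2 / 0.5 = 8.32, df 1 and 50, power 0.807. At N = 50 power is 0.791. So N = 52, or 26 per group, as stated.
- m = 4, N = 36: λ = 0.04 × 36 × 4 / 0.5 = 11.52, df 3 and 102, power 0.807. At N = 34 power is 0.781. So N = 36, which agrees with the remark that four time points need fewer.

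Both statements in the article match the classical F-test.

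**2. Who would be left out of the 2*4 analysis?**

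- Planned drop-out alone: 60 × 0.10 = 6 excluded, 54 kept.
- A missed pedometer week removes a participant just as drop-out does. With independent misses at three follow-ups (assumed rates), complete rows number 60 × 0.95³ = 51.4 at 5% per visit and 60 × 0.90³ = 43.7 at 10% per visit.
- The 2*2 analysis needs only baseline and 4 months, so later loss does not touch it.

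**3. How large could the bias be?**

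Assumptions: outcome SD 1 at each visit; all correlations 0.5; true late effect 0.40 SD; loss occurs after the 4-month visit; control loss is random; intervention loss is likelier when the 4-month change z is poor. Loss is p in each arm.

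- Variance of change from baseline: 2(1 − 0.5) = 1.
- Covariance of 4-month and late change: 0.5 − 0.5 − 0.5 + 1 = 0.5, so the regression slope is 0.5.
- Completers' late estimate = 0.40 + 0.5 × E(z | stays), with z centred at the intervention-arm mean.

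*Threshold mechanism* (half of the lowest 2p of changes leave): E(z | stays) = 0.5 φ(z₂ₚ) / (1 − p).

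- p = 0.10: 0.5 × 0.280 / 0.90 = 0.156; estimate 0.40 + 0.078 = 0.478.
- p = 0.17: 0.5 × 0.366 / 0.83 = 0.221; estimate 0.40 + 0.110 = 0.510.

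*Logistic mechanism* (log-odds of loss = a − b·z, with a set to give p; numerical integration):

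| Loss p | b = 0 (random) | b = 1 | b = 2 |
|---|---|---|---|
| 10% | 0.400 | 0.445 | 0.471 |
| 17% | 0.400 | 0.474 | 0.513 |

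The completers' estimate is thus about 0.44 to 0.48 at 10% loss and 0.47 to 0.51 at 17%. In a simulation of the threshold case at 10%, 20% and 30% loss, the completers gave 0.48, 0.52 and 0.55 and a likelihood estimate gave 0.40 to 0.41.

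*Opposite direction.* If loss follows poor change by the same rule in both arms, the control arm loses more people. With 10% loss overall, b from 1 to 2 and a true 4-month effect of 0.40 or 0.80, the completers' late estimate is 0.34 to 0.39, below the true 0.40.

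**The case against.** The strongest reply is that no sentence says incomplete participants are excluded. The Analysis section speaks of a mixed design; the word ANOVA appears only in the sample-size text. Imputation before the ANOVA, or a linear mixed model, would fit the Analysis wording, and the intention-to-treat label points that way. Handling of missing values is commonly left to a fuller protocol or analysis plan, which is not shown. This stands. A reader might infer that the 2*4 analysis simply is a completers' analysis, or that the article openly contradicts itself. The document does not support that: exclusion follows only if the named ANOVA is run on unimputed data. Silence on missing data is not the point here; the point is that the method that is named does not deliver the principle that is claimed.

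The 4-month result is also protected. It has its own 2*2 analysis, so distortion of the 4-month cell within the 2*4 layout matters little.

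The bias is modest beside the pilot's imprecision: a standard error of 0.285 SD, taken from a simulation with 30 per arm and 19% random loss, gives a 95% interval of about ±1.96 × 0.285 = ±0.56 SD. The comparison also favours the mixed model by construction, because the simulated loss depended on observed 4-month change. If loss depends on later walking that was never recorded, the mixed model is biased too. Both remarks are fair, and they limit the size of the claim.

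Two further readings should be resisted. The first is that the trial loses its power: with 54 complete rows and ρ = 0.5, power is 0.82 for the 2*2 test and 0.95 for the 2*4 test. The second is that the 2*4 F-test is invalid for lack of sphericity: a standard correction is routine detail that the article neither states nor excludes.

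**Conclusion.** The point holds in conditional form and for the long-term analysis only. The article claims intention to treat, names a mixed ANOVA for four time points, and expects 60 to become 54. Unless values are imputed or a likelihood model is used, the 2*4 analysis describes completers.

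If loss is completely at random there is no bias. If intervention-arm loss follows poor 4-month change, a true late effect of 0.40 SD is overstated by about 0.04 to 0.08 at 10% loss and 0.07 to 0.11 at 17%. If the same rule acts in both arms, the effect is understated. These figures rest on the assumed correlation of 0.5 and the assumed loss mechanisms; the article gives neither. The point is worth acting on because the remedy is cheap and the maintenance estimate is one of the things the pilot is meant to supply.

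**What to change.** For the long-term outcome, name a linear mixed model for repeated measures in place of the mixed ANOVA:

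- Include all randomised participants with any pedometer week, in the group to which they were allocated.
- Fit group-by-visit effects with an unstructured covariance over visits. Treat baseline steps as one of the outcomes or as a covariate; the first choice also keeps anyone whose baseline week is missing.
- Report the group difference at 4 months, 1 year and 2 years, each with its interval and the number contributing at that visit.

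If the mixed ANOVA is kept, the plan should say how missing weeks are imputed before it is run; otherwise it should call the 2*4 result a completers' analysis.

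The cost is a change of analysis wording and a standard procedure in any package. No extra data are needed, and the sample size need not change. The downside is reliance on missing at random, which is weaker than the completer ANOVA's need that completers represent everyone randomised.

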### Outcome Measures

Measures will be taken for participants in both arms of the study, at baseline, 4 months, 1 and 2 year follow-ups. All questionnaires will be administered by the researcher.

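### For the baseline-to-4-month comparison, the 2×2 mixed ANOVA tests raw change scores; it is valid, but adjusting for baseline steps would be more precise at almost no cost

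*Protocol article*

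**What the plan says.** The Analysis section of the protocol article specifies a "repeated measures mixed design (2 groups*2 time points for short-term outcome, and 2 groups*4 time points for long-term outcome". No baseline covariate is mentioned; baseline enters the model as one of the repeated outcomes.

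The sample-size paragraph under Recruitment uses the same model: GPower3 was used "to carry out a (2) group by (2) time mixed ANOVA to detect a small effect size (0.2) with an alpha of 0.05". At the chosen 80% power, this gave 26 per arm. The comparison that set the trial's size is the "conservative initial (2) time point (baseline to 4 month) mixed ANOVA" of the primary outcome, mean daily pedometer steps.

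Baseline steps will be available in both arms. Outcome Measures states: "Measures will be taken for participants in both arms of the study, at baseline, 4 months, 1 and 2 year follow-ups". The article gives no SD for step counts and no correlation between visits.

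**The concern.** A 2 group by 2 time interaction compares the arms on 4-month minus baseline steps. That fixes the coefficient of baseline at 1, whatever the data show. ANCOVA estimates the coefficient instead. In a randomised trial it targets the same between-arm difference, because the expected baselines are equal, and apart from one degree of freedom it is no less precise.

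Precision matters here because the pilot's declared purpose is to supply an effect size for a multi-centre trial, from about 54 completers (60 recruited less 6 expected drop-outs). A wider interval than the data require is passed straight into the planning of the next study.

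**Working it through.** **Inputs.** From Recruitment: effect size 0.2, α = 0.05, power 80%, 26 per arm (52 in total), and 60 recruited with 6 drop-outs, which leaves 54 or 27 per arm. Assumed because not stated: ρ, and equal SDs at the two visits (relaxed in step 5).

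**1. Reproduce the plan's figure.** For the within-between interaction in GPower form, λ = f²·N·m/(1−ρ), with m visits, 2 groups, and degrees of freedom (m−1) and (N−2)(m−1). With f = 0.2, m = 2, ρ = 0.5 and N = 52, λ = 0.04 × 52 × 2 / 0.5 = 8.32 on 1 and 50 df, and power is 0.807. This is the smallest even N that reaches 80%, so 26 per arm is reproduced. Other values of ρ give a different total: 72 at 0.3, 62 at 0.4, 42 at 0.6, 32 at 0.7. With m = 4 and ρ = 0.5 the total is 36, which agrees with the statement that "A (4) time point mixed ANOVA sample size calculation required fewer participants in the study". The article does not say in words that the interaction is the test, but this reading reproduces its number.

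**2. Put the effect on the SD scale.** For a t test on change, λ = (N/4)·d²/[2(1−ρ)]. Setting this equal to 2f²N/(1−ρ) gives d = 4f = 0.8 outcome SDs.

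**3. Compare variances** (outcome SD = 1, n per arm).
- Change score: (2/n) × 2(1−ρ)
- ANCOVA: (2/n) × (1−ρ²)
- Ratio, ANCOVA to change score: (1+ρ)/2, so the information lost is (1−ρ)/2.

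A simulation of 4,000 trials with 26 per arm gave ratios of 0.76 at ρ = 0.5 and 0.91 at ρ = 0.8, against 0.75 and 0.90 by formula. Both estimators were centred on 0.8.

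**4. Results at 54 completers, difference 0.8 SD.**

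| ρ | Variance ratio | Information lost | Reduction in SE | Power, change score | Power, ANCOVA |
|---|---|---|---|---|---|
| 0.3 | 0.65 | 35% | 19.4% | 0.684 | 0.856 |
| 0.4 | 0.70 | 30% | 16.3% | 0.750 | 0.882 |
| 0.5 | 0.75 | 25% | 13.4% | 0.822 | 0.915 |
| 0.6 | 0.80 | 20% | 10.6% | 0.897 | 0.950 |
| 0.7 | 0.85 | 15% | 7.8% | 0.961 | 0.981 |
| 0.8 | 0.90 | 10% | 5.1% | 0.995 | 0.998 |
| 0.9 | 0.95 | 5% | 2.5% | 1.000 | 1.000 |

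At ρ = 0.5 the 95% half-width falls from 0.546 to 0.473 SD. The gain equals analysing 54/0.75 = 72 participants by change score. Equivalently, ANCOVA needs 40 in total for 80% power where the mixed ANOVA needs 52.

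**5. Unequal SDs.** Let the follow-up SD be k times the baseline SD. The variances are then proportional to 1 + k² − 2ρk (change) and k²(1−ρ²) (ANCOVA). Their difference is (1−ρk)², which is never negative. With k = 1.3 (an assumption) and ρ = 0.5: 1.2675/1.39 = 0.91, a loss of 9%. With ρ = 0.7: 0.8619/0.87 = 0.99, a loss of 1%. With k below 1 the loss can exceed (1−ρ)/2.

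**The case against.** The strongest reply is that nothing here is wrong. The planned test is unbiased under randomisation, the sample-size and Analysis sections agree with each other, and with 54 completers the power is 82% on the plan's own assumptions, above the 80% target. That stands, and it limits the point to a recommendation. It does not remove it, because the model is fixed in two places and a more precise one is available from data already being collected.

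Three stronger readings are tempting, and the documents do not support them.

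- **That a quarter of the precision is lost outright.** The article never states ρ. The value 0.5 is recovered from the sample size, so it is a planning input and not evidence about step counts. The quarter is also on the variance scale and assumes equal SDs.
- **That the four-visit analysis loses the same amount.** The 2×4 interaction has 3 degrees of freedom and is not a change-score test. Neither the equivalence nor the 25% carries over.
- **That the change score is biased because allocation precedes the baseline visit.** The Design section does place allocation before the researcher's first contact. Suppose that produced a baseline shift b between arms. If it vanished by 4 months, the bias would be b for the change score and ρb for ANCOVA. If it persisted, the bias would be 0 and (1−ρ)b, and the ordering reverses. The article does not say which case would apply, so this gives no ground for preferring either method.

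**Conclusion.** The point holds as an efficiency improvement for the baseline-to-4-month comparison only. At the ρ = 0.5 implied by 26 per arm, and with equal SDs, the planned test gives up 25% of the information. The loss would be small if step counts prove highly correlated between visits, or if the spread grows by follow-up. Under randomisation, ANCOVA is no less precise at any ρ or SD ratio, one degree of freedom apart. The direction of the recommendation is therefore secure even though its size is not.

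**What to change.** In the Analysis section, make the short-term primary analysis an ANCOVA of 4-month mean daily steps on group and baseline mean daily steps. Report the adjusted difference in steps with its 95% CI. Analyse the other continuous outcomes at 4 months in the same way, each with its own baseline as covariate.

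Report the observed baseline-to-follow-up correlation as well. Step 1 of the working shows why the larger trial needs it: the same effect size of 0.2 requires 72 participants at ρ = 0.3 and 32 at ρ = 0.7.

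In the sample-size paragraph under Recruitment, add that 26 per arm was derived for the mixed ANOVA and is conservative for the ANCOVA, so that the two sections stay consistent.

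The cost is a wording change in two sections and one degree of freedom. No new data or participants are needed.

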### Evaluation

The effectiveness of the intervention will be determined through analysis of the outcome variables listed above. Analysis of the primary outcome variable will determine whether the brief psychological intervention group have increased walking in comparison with the control group. The psychological measures will be analysed to determine whether improvement in walking is mediated by changes in illness and walking beliefs.

On completion of the study, participants in the intervention group will be asked additional semi-structured questions about their experience of the intervention including what they thought of their action plan, whether they followed their action plan, whether the barriers they predicted prevented them from following their action plan, whether they used their coping plan, whether they intend to follow their action plan in the future, and whether they thought it was worthwhile to take part in the study.

## Discussion

A brief psychological intervention which increases walking in claudicants may (a) reduce the demand for surgery for patients with intermittent claudication; (b) reduce costs for the NHS; (c) be accessible and acceptable for patients and lead to long term behaviour change; (d) encourage patient self-management of their chronic condition; and (e) increase patient quality of life.

This trial is novel in that previous interventions to increase walking in claudicants have either relied on the provision of advice, which does not overcome barriers to walking for claudicants; or supervised exercise programmes, which are not commonly available and which may not be an acceptable means of intervention for many claudicants for a variety of psychological and environmental reasons. This is the first time a psychological intervention based on the CSM has been carried out to increase walking in patients with intermittent claudication. The intervention is patient-centred, can be tailored to the specific needs of each individual, and has directly measured behaviour change (walking) as the primary outcome. A health economic evaluation would be central to any subsequent large-scale trial.

A clear theoretical framework underpins the intervention, and the content of the intervention is clearly specified and based on thoroughly tested and evidenced health psychology techniques. The intervention is capable of being delivered by trained non-specialist health workers in an NHS setting.
